since the previous morning, the presence of malaria will be assessed by the Rapid Diagnosis Test and treated according to the national guidelines as indicated. The field workers will be trained to recognize dehydration and other danger signs, and to refer all children with dehydration, dysentery, fever, or persistent diarrhea to the local health clinic for medical evaluation. Serious adverse events that are determined by the study physicians to be “related” or “likely related” to the study intervention will be reported immediately to the principal investigators, who will notify the chairs of their respective Institutional Review Boards. Serious adverse events that are determined by the study physicians to be “unlikely related” to the study intervention will be reported to the principal investigators on a monthly basis and summarized for the Institutional Review Boards in yearly progress reports.

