The LNS will be delivered in plastic pots containing 140 g (sufficient for one week) or sachets containing 20 g (the dose for one day) and labeled individually with one of 8 color codes (two colors per treatment group) to avoid the possibility of any mix-ups during delivery to the household. The child's caregivers will be provided with a measuring spoon and advised to feed the day's allotment (20 g = 2 spoonfuls) in two servings at meal times (1 spoonful per each of two meals). In particular, the caregiver will be requested to add 1 spoonful of LNS to ~2 tablespoons of cereal porridge or other complementary food and then to continue feeding any desired additional amount of the food. This is to maximize the likelihood that all of the prescribed LNS dose will be served each meal.

All mothers will be encouraged to continue breastfeeding on demand.

The LNS will be produced and packed by Nutriset (Malaunay, France). Raw ingredients include peanut paste, dried skimmed milk, maltodextrin, sugar, vegetable oil, and a mineral and vitamin mix. The products are packed in opaque, plastic containers, each containing 140 g of the supplement or foil sachets containing 20 g of the LNS. LNS containers will be stored in the Bama field office at a temperature between 20°C and 40°C. At these temperatures, the nutritional quality is guaranteed for 12 months. Because of low water activity, the products are resistant to microbial contamination. The specific nutrient content of each is summarized in Table 2.

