### Frequency of analyses

The main statistical analysis will be done after the last participant attains the age of 18 months and the main intervention is completed. First the dataset will be checked for outliers. Then participants will be assigned to their respective treatment group to allow group-wise analysis. The randomization code revealing the identity of the assigned group will be broken only after the statistical analysis of the main outcomes is completed and only after consulting among all investigators. A further analysis will be done at the end of the follow-up, i.e., when all children reach 42 months of age.

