#### Plan for reporting adverse and serious adverse events to the IRB

All suspected adverse events are documented according to standard operating procedures devised in conjunction with the Institutional Review Boards at IRSS,B and the University of California, Davis. Suspected serious adverse events that are determined by the study physicians to be "related" or "likely related" to the study intervention are immediately reported to the principal investigators, who will notify the chair of the respective Institutional Review Boards. Serious adverse events that are determined by the study physicians to be "unlikely related" to the study intervention will be reported to the principal investigators on a monthly basis and summarized for the Institutional Review Boards in yearly progress reports.

Data will be collected for suspected adverse events during the intervention period from enrollment to 18 months of age in the intervention groups . Potential adverse reactions to study foods are elicited with structured forms at the weekly home visits. Serious adverse events include all untoward medical occurrences that result in death, are life-threatening, require inpatient hospitalization, result in persistent or significant disability, or are otherwise considered a serious medical condition by a study physician. Information on the causes of death will be collected by a verbal autopsy method.

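### Deaths and other SAEs judged unlikely related reach the review boards only yearly, and the protocol states no safety exception to the sealed code and no by-arm view of them while children are on product

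*Protocol*

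**What the plan says.** The protocol gives the reporting rule twice, in the same terms: under the plan to monitor data for subject safety and under the plan for reporting adverse events to the IRB.

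- **Fast route.** Events that study physicians judge related or likely related go at once to the principal investigators, and from them to the board chairs.
- **Slow route.** Events judged unlikely related "will be reported to the principal investigators on a monthly basis and summarized for the Institutional Review Boards in yearly progress reports".
- **Scope.** "Serious adverse events include all untoward medical occurrences that result in death, are life-threatening, require inpatient hospitalization". A death therefore follows whichever route the causality judgement sends it down.

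The section on frequency of analyses fixes when arms can be compared. "The main statistical analysis will be done after the last participant attains the age of 18 months and the main intervention is completed". Children are then sorted into groups, after an outlier check. "The randomization code revealing the identity of the assigned group will be broken only after the statistical analysis of the main outcomes is completed", and all investigators must first be consulted. No exception for safety is given.

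The only stated comparison of deaths by arm is a Fisher's exact test across the four intervention groups (Data entry and analysis), with no interim use. The text at hand names no monitoring committee, no interim safety look and no independent holder of the code.

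**The concern.** How fast a board hears of a serious event depends on a case-by-case causality judgement about a masked product. In this population the serious events to expect are malaria, diarrhoea and respiratory infection, which the trial already tracks weekly. One such death will rarely look product-related, so it will usually take the slow route. If a zinc dose shifted the frequency of these background events, the shift would appear in counts by arm and not in any single case. The second main objective asks how zinc dose affects morbidity, so an effect in either direction is within the trial's own question.

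At stake is whether anyone responsible for the children would have grounds to act while supplementation is still under way. The delayed group is also affected. Its children start LNS with 10 mg zinc at 18 months of age, and the earliest of them could do so before the last participant reaches 18 months, which is when arms are first compared.

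**Working it through.** There is no stated figure to reproduce. The point rests on setting the rules side by side; the arithmetic only illustrates their consequence.

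**1. The rules together**

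| Question | Answer in the protocol |
|---|---|
| Who hears of a death judged unlikely related? | Principal investigators monthly; boards yearly |
| Must those reports be split by arm? | Not stated |
| When are children first grouped? | At the main analysis, after the last child reaches 18 months |
| When may the code be opened? | Only after the main outcomes are analysed |
| Is there a safety exception? | None stated |

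The board interval is 12 months and exposure is 9 months per child (Interventions), so a child's whole course can fall between two board reports.

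**2. Timeline (illustrative)**

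Inputs: about 2440 intervention children, 610 per group (Subject selection); recruitment from April 2010 and data collection to the end of June 2012 (Location and duration), which is 27 months. Assumptions: data collection ends with the last 18-month visit, accrual is uniform, and the yearly reports count from first enrolment. Accrual A is then 27 − 9 = 18 months. That section also gives about 48 months for data collection, so A is an inference; A = 24 is shown as an assumed alternative.

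Share of all supplementation child-months elapsed (denominator 9A):

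- Month 6: (6²/2)/(9A) = 18/162 = 11% for A = 18; 18/216 = 8% for A = 24.
- Month 12: children enrolled in the first 3 months have completed (3 × 9 = 27) and the next 9 months' enrolments are part-way (9²/2 = 40.5). 67.5/162 = 42%; 67.5/216 = 31%.
- Month 24: for A = 18, 15 × 9 + 3 × 7.5 = 157.5, and 157.5/162 = 97%. For A = 24, 135 + 40.5 = 175.5, and 175.5/216 = 81%.

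By the second yearly report, roughly 80% to 97% of exposure would be past.

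**3. What a pooled count shows**

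The protocol gives no mortality rate. Assume p = 0.5%, 1% or 2% over nine months. The total with no arm difference is 2440p. With one arm doubled it is 610p × 5.

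| p | No difference | One arm doubled | Increase ÷ √(no difference) |
|---|---|---|---|
| 0.5% | 12.2 | 15.3 | 3.05/3.49 = 0.9 |
| 1% | 24.4 | 30.5 | 6.1/4.94 = 1.2 |
| 2% | 48.8 | 61.0 | 12.2/6.99 = 1.7 |

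The increase is between 0.9 and 1.7 Poisson standard deviations, and no expected rate is stated to compare it with. A total that is not split would hardly reveal the excess.

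**4. What a split count shows**

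Power of a two-arm Fisher test at the end, 610 v 610, two-sided 5%, ignoring clustering by concession:

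| p | One arm doubled | One arm tripled |
|---|---|---|
| 0.5% | 9% | 31% |
| 1% | 22% | 65% |
| 2% | 48% | 94% |

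Mid-trial counts are smaller still. At p = 1% and A = 18, about 24.4 × 0.11 = 2.7 deaths in all by month 6 and 24.4 × 0.417 = 10.2 by month 12. A split makes a large imbalance visible for judgement. It is no basis for a formal test.

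**The case against.** The strongest reply is that oversight exists. The principal investigators receive every unlikely-related SAE monthly, reactions are sought at weekly visits, causes of death are collected by verbal autopsy, and seriously ill children are withdrawn. The code-breaking sentence sits in a section that times the statistical analysis, and it does not expressly forbid a masked safety tally. Adverse events are also handled under operating procedures agreed with the review boards, which are not shown and could provide for by-arm review or emergency unmasking.

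Much of this stands. A reader might infer that an excess cannot be seen in time, that no board or investigator could act, or that the boards could never learn the product after a related event. The documents do not support readings that strong: monthly reports do reach people able to act, and the unseen procedures may fill part of the gap. What remains is that the protocol itself states no by-arm route. Monthly case reports and individual withdrawals do not show a difference between arms. Any procedure allowing early unmasking for safety would conflict with the code-breaking sentence as worded.

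It is also fair that a by-arm tally is a limited tool. Counts would be sparse, and compiling them inside the team could weaken masking. A tally cannot show a harm common to all LNS arms. The one product risk the protocol names, iron in a malarial area, is of that kind, since all three LNS formulations contain 6 mg (Table 2). The delayed group cannot supply the contrast during the trial, because adverse events are collected in the intervention groups only.

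**Conclusion.** The point holds in this form: the protocol sends deaths and other SAEs judged unlikely related to the boards only yearly, defers grouping to the main analysis, and seals the code until after it without a safety exception. It therefore states no route by which an excess in one arm would be seen by arm, or a product identified for safety, while children are on it. It does not follow that nobody could notice or act.

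The firm figure is the 12-month board interval against a 9-month course. The exposure shares (31% to 42% at the first yearly report, 81% to 97% at the second) are illustrative and rest on uniform accrual over an inferred 18 or assumed 24 months. The death counts rest on assumed mortality of 0.5% to 2%. This is a recommended safety change; it does not affect the validity of the planned efficacy comparisons.

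**What to change.** 1. **Safety monitoring and IRB reporting sections.** Report every death and every life-threatening SAE promptly to the board chairs, whatever the causality judgement. Cost: wording in two places and, at the assumed mortality, prompt notice of about 12 to 49 deaths over the trial, plus life-threatening events.
2. **Frequency of analyses.** Add that a named key holder outside the analysis and field teams may open the code for an individual or a group for safety reasons, without disclosure to the analysis team. Check the operating procedures against this wording. Cost: one sentence and one named role.
3. **Optional.** Have someone outside the analysis team tally deaths and hospitalisations by masked group, with numbers at risk, at an interval shorter than 9 months. Two colours per group mean a colour count cannot be collapsed to groups without the key, so the key holder would supply neutral group labels. Data already move weekly to the coordinating office. State that the tally aids judgement and is not a stopping test. State the downsides too: sparse counts, possible false alarms, some risk to blinding, and no view of a harm shared by all LNS arms.

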## **RESOURCES TO CONDUCT THIS STUDY**

The project is fully supported by a grant from the Bill and Melinda Gates Foundation. To implement this program and ensure the ultimate application of the research findings, a consortium, the iLiNS study group, has been formed among researchers from Burkina Faso, Malawi, Ghana, Finland, France, and the United States. These groups have complementary expertise in the technical aspects of zinc nutrition, implementation of community-based nutrition and disease treatment programs, and evaluation research. Specifically, technical experts from the Program in International and Community Nutrition (PICN) of UC Davis, Helen Keller International, and the Institute of Research in Health Sciences (Institut de Recherche en Sciences de la Santé - IRSS) in Bobo Dioulasso, Burkina Faso will collaborate on the design, implementation, and evaluation of this project.

UC Davis will provide administrative, financial and technical oversight. A post-doctoral research fellow in International and Community Nutrition will be present at the field site, serving as field nutrition coordinator throughout the period of data collection; and the Statistician of the PICN will assist with data analysis and the preparation of final statistical models. A sub-contract will be prepared with IRSS, Bobo-Dioulasso, which will be responsible for implementation of the field work, including recruiting and hiring of the field research team, data entry and processing, and laboratory analyses. The core study team will coordinate the day-to-day management of the study out of the field office at the Dandé District Hospital. Technical experts from International Zinc Nutrition Consultative Group (IZiNCG), which is housed administratively within UC Davis and based physically in the HKI regional office in Dakar, Senegal, will assist in ensuring quality control of the zinc analyses, and will assist with dissemination of the results of the study and subsequent advocacy with the Ministry of Health in Burkina Faso. Supervision will be provided through regular field visits and conference calls by the senior investigators and principal investigators of the study team. [name], who is presently based in Dakar, where he also serves as the HKI Africa Regional Advisor for Nutritional and Child Survival, will be able to make frequent supervisory visits to the field site in Burkina Faso.

Nutriset S.A.S. has developed and will produce the lipid-based nutrient supplements (LNS) and zinc/placebo supplements used in this trial. It will also be responsible for the quality control of the products.

The IRSS,B is equipped with the following facilities and equipment:

- High speed internet connection with WIFI
- Mono and bi-distillation machine
- Millipore Direct-Q: ultra pure water
- Autoclave
- Nutrition/Chemical: HPLC, Atomic absorption spectrophotometer, FTIR
- Serological: ELISA reader, beta counter and luminescence
- Radioimmunoassay: hybridization oven, beta counter
- Parasitology: microscopes
- Insectarium
- Chemical room for plant compound extraction
- Cell culture room with hoods, incubator, centrifuges, cell harvester
- Molecular biology: thermocyclers, electrophoresis, photo documentation system

**RISKS:**

The risks involved in this study are minimal. Although nutritional status can be assessed by clinical examination, biochemical assessment was selected because it permits assessment of multiple micronutrients over the full range of adequate status to mild, moderate, or severe deficiency.

Blood draws can cause momentary pain and discomfort and can result in bruising, but rarely result in infection or other complaints. Blood draws will be performed by qualified health professionals. Two capillary blood samples will be collected from all subjects at ages 9 and 18 months. In a sub-set of subjects, two 5-ml venous blood samples will be collected when participants are 9 and 18 months old. The collected volume represents <1% of the child's total blood volume and is replaceable from the child's own blood production within a day; the total volume of blood collected (10 ml) is minimal and unlikely to result in any adverse effects.

The study poses risks of psychological harm to participants as a result of inadvertent lack of respect for cultural norms, which is likely to be unpleasant but temporary. The risk will be minimized by consulting with local community leaders prior to the start of the study, and obtaining their permission to recruit subjects in their villages. IRSS,B, established in 1997, has developed excellent rapport with local community leaders and residents. Additionally, the majority of the study team members are from Burkina Faso and have extensive field experience that will be shared during training.

There is a risk of accidental release of personal health information which may have important social or psychological consequences for the subject. This risk will be minimized by the confidentiality measures described below.

Plan for protecting subject privacy and confidentiality.

Subject data will be identified with unique identification numbers, and full names will not be attached to the data. All documentation regarding the participants, including the laboratory samples, source data and the Adverse Event Form will be identified with appropriate participant codes, both on paper and in computer files. The full names will only appear on informed consent forms and a separate coding list.

The investigators shall maintain the regulatory documents (informed consents, ethical approval) until participants reach the age of 25 years. Selected data (participants' name, home village, household identification number, enrollment date, and enrollment number) will be summarized in an electronic database and a paper participant register. The registers will be stored in a locked space at the study office. Data from these registers may be given only to authorized members of the research team and authorities guiding health research in Burkina Faso and at the University of California, Davis.

Subject names will not be included in any data entry or reporting of results. Blood collection will be completed in a private area of the health center to ensure subject privacy. Additionally, interviewers will request that only the respondents be present during the interviews conducted during home visits. Subject privacy and confidentiality practices will be addressed during training of all study personnel.

#### Plan for reporting adverse and serious adverse events to the IRB

All suspected adverse events are documented according to standard operating procedures devised in conjunction with the Institutional Review Boards at IRSS,B and the University of California, Davis. Suspected serious adverse events that are determined by the study physicians to be "related" or "likely related" to the study intervention are immediately reported to the principal investigators, who will notify the chair of the respective Institutional Review Boards. Serious adverse events that are determined by the study physicians to be "unlikely related" to the study intervention will be reported to the principal investigators on a monthly basis and summarized for the Institutional Review Boards in yearly progress reports.

Data will be collected for suspected adverse events during the intervention period from enrollment to 18 months of age in the intervention groups . Potential adverse reactions to study foods are elicited with structured forms at the weekly home visits. Serious adverse events include all untoward medical occurrences that result in death, are life-threatening, require inpatient hospitalization, result in persistent or significant disability, or are otherwise considered a serious medical condition by a study physician. Information on the causes of death will be collected by a verbal autopsy method.

#### Use of placebo

This study involves the use of a placebo because of the possibility of "regression to the mean", whereby individuals with lower initial plasma zinc concentrations, morbidity or growth status subsequently have higher ones and *vice-versa*. Therefore, it will be possible to interpret the effects of supplementation only if there is a placebo comparison group.

The purpose of the delayed intervention group is to control for possible functional responses to LNS that does not contain added zinc and/or a "Hawthorne effect" due to the presence of the study team, either of which could affect growth rates independently of LNS and zinc.

#### **BENEFITS:**

All participants will receive free food supplements during the intervention or delayed intervention periods. Approximately three-fourths of the participants will receive free food supplements (LNS) between 9 and 18 months of age and the rest will receive free food supplements (LNS) between 18 and 27 months of age. All participants will further benefit from assessment of nutritional status and referral for treatment by usual services when necessary.

All participants receive the benefit of learning whether or not they are anemic. Each subject will be given their hemoglobin value immediately after their blood is collected. Staff will explain whether their hemoglobin is in a normal range or low (anemic) range and refer subjects with severe anemia to the health center for treatment.

Participants in the intervention groups will benefit from weekly morbidity surveillance and selected treatment or referral, as indicated, from 9 to 18 months of age. If needed, the research team will give the participants in the intervention groups treatment for specific illnesses or refer them for treatment at the local health center for specific serious health conditions. All participants who are found to have a blood hemoglobin concentration below 50 g/l will be referred for blood transfusion according to national treatment guidelines and excluded from the study. Participants with hemoglobin between 50 and 79 g/l will be treated for anemia (iron syrup and Mebendazole) free of charge.

Aside from receiving LNS and zinc supplementation, assessment of health and nutritional status, and referral for treatment when necessary, there is no other direct benefit to the subject.

